### Study Procedures

Following enrollment, participants will complete baseline measures (T1) and then be assigned to either the experimental or the control group. An RC will then contact the statistician via telephone or email to obtain the group assignment within 48 hours. The participant will be informed of the group assignments, and the trainer will be given the participants’ contact information to schedule the training sessions and assign the control group. The training will be scheduled after completing the blinded postintervention data collection (T2). In an effort to minimize bias, a research assistant (RA) will be blinded to group allocation and participants will be instructed not to discuss their program with the RA. The RC will also arrange for the blinded follow-up (retention) data collection for all participants 3 months after postintervention data collection (T3). Qualitative interviews will be conducted by the RC by phone or videoconferencing within 7 days of completing the intervention. Given the self-report nature of the primary outcome, the interdisciplinary experience of 3 study investigators with RCTs who are not located at the data collection site, and the involvement of a citizen partner and Muscular Dystrophy Canada in data collection, analysis, and interpretation, a data monitoring committee was not established. Participants in the intervention and control groups will continue to receive usual care (if any) during the study. The trial design describing coordination, testing, and experimental procedures is depicted in Figure 1.

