### Intervention Details

According to the evidence-based Wheelchair Skills Training Program (WSTP) [29], participants will receive 5 individual 45-minute weekly wheelchair skills training sessions. As previously described by Best et al [26], the training sessions will take place in the community, in and around the participants’ homes and neighborhoods (eg, libraries, shopping centers, museums, and parks), and will be customized according to the participants’ goals. The WSTP provides suggestions for individualizing the approach based on the learner’s impairments (ie, weakness, spasticity, contractures, cognitive impairments, and movement disorders like ataxia, tremor, and chorea). Therefore, specific training considerations can be made regardless of diagnosis. The WSTP sessions will begin with a 5-minute review of goals/progress, followed by a 10-minute warm-up (wheeling activities, random practice of previously learned skills). This will be followed by 20 minutes of attempting new skills, with training on each skill carried over to the next session until the skills are learned or the trainer and participant mutually agree to stop training. The trainer will periodically ask the participant to practice newly learned skills to incorporate variability of practice. Finally, a 10-minute cooldown will take place, during which the participant will practice skills in a self-controlled environment.

The trainer (author EN), a graduate student with training in physiotherapy will receive two 4-hour sessions by experts in manual wheelchair skills training (authors [name], FR, and [name]), which has been shown to improve knowledge and confidence for training wheelchair skills [30]. The trainer will also complete self-guided learning modules, semistructured practice with trained trainers, and the Wheelchair Skills Program Certification Exam [31]. The fidelity of the WSTP administration will be evaluated by a member of the study team not involved in testing or training who will attend 1 training session per participant (randomly throughout the training period). The trainer will also complete a detailed training log, a checklist of standardized steps to be followed during training, and document adherence to the intervention and any adverse events. Formative assessments with the trainer will ensure fidelity.

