### Qualitative Interviews

The participants will complete semistructured individual interviews lasting between 45 and 60 minutes, either in person or online with the RC, after completing the WSTP intervention. The interview guide will be created by the study team using an iterative process following an appropriate framework (eg, International Classification of Functioning, Disability, and Health) [32]. Questions will explore expectations with wheelchair use, previous experiences with using a wheelchair, and perceptions of wheelchair skills training. In addition, we will explore perceptions of the WSTP (dosage, fatigue, training approaches, and usefulness), experiences with manual wheelchair service provision, satisfaction with manual wheelchair use, and social participation. The interview guide will be pilot tested with 1 person with ARSACS and 1 person with MD1. The interviews will be audio recorded.

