### Data Analysis

Summary statistics (means, standard deviations, frequencies, and percentages) will be used to describe the sample. Details of adherence and intervention fidelity will be summarized. Assumptions for parametric testing of quantitative data will be verified, and the data will be screened for outliers [45]. An intention-to-treat analysis will be prioritized (with a per-protocol analysis reported depending on adherence and fidelity), and missing data will be addressed using multiple imputation methods for repeated measures of longitudinal data [46].

To address the primary objective, T2 WST performance scores will be compared between the experimental and control groups using ANCOVA or its nonparametric equivalent, with baseline scores used as the covariate. Variance (*R*^2^), statistical significance (95% CI), and effect sizes (partial η^2^) will be assessed using sums of squares methods. Secondary objectives will be evaluated using linear mixed-effect models, which are flexible to explore within-participant mixed/random effects [47].

Post-hoc exploratory analyses will investigate the influence of age, gender, diagnoses (ataxia or dystrophy), and manual wheelchair experience on effect size using linear mixed-effect models. Comparisons between WST-Q-M within-participant change scores for the experimental group (T1-T2) and WST-Q-M within-participant change scores after training in the control group (T2-T3) will be explored using *t* tests. Sensitivity analyses will be conducted on demographic variables (eg, age, sex, gender, and diagnoses) to generate hypotheses and inform future investigations.

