A reflexive thematic analysis will be used to explore perceptions of the influence of manual wheelchair training on mobility, participation, and quality of life according to an appropriate framework (eg, International Classification of Functioning, Disability, and Health) [48]. Interviews will be transcribed verbatim, and researchers will familiarize themselves with the data by rereading and relistening to interviews. Using NVivo software (version 14; Lumivero), transcripts will be coded line-by-line. Then, the codes will be grouped into similar ideas, and themes will be developed using an inductive approach. Member checking will be performed with participants throughout data analysis, with the citizen partner actively involved in data interpretation and synthesis to enhance confirmability. Final themes and subthemes will be verified with participants and the research team. To further enhance trustworthiness according to Ahmed (2024) [49], the credibility of data interpretation will be strengthened through triangulation with quantitative data. Quantitative and qualitative data will then be integrated using joint display diagrams to merge, compare, and relate findings to better understand how subjective perceptions align with measured improvements [50]. We will also explore why some participants may experience better outcomes or how people deal with challenges. Additionally, we will remain aware of potential personal biases regarding our perception of the effectiveness of the intervention. Finally, findings on the facilitators and barriers to training may be transferable to individuals with other neuromuscular disorders who share similar symptoms and functional characteristics [49].

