A multifaceted knowledge translation strategy will be used to increase awareness and knowledge to change practice for manual wheelchair skills training for people with ARSACS and DM1. Targeted materials for health care professionals will include infographics, podcasts, and video capsules that will be launched through the international PROSPAX (Progression Chart of Spastic Ataxias) initiative on recessive ataxias and neuromuscular disorders ([name]), including Rare Disease Day. Materials will be shared through clinical and community platforms including websites and social media of Muscular Dystrophy Canada, Groupe de Recherche Interdisciplinaire sur les Maladies Neuromusculaires, and the Wheelchair Skills Program. Lunchtime presentations and manual wheelchair training workshops will be planned with clinicians. Academic dissemination will include a minimum of 2 peer-reviewed articles and 2 national/international conferences. Led by the corresponding author ([name]), all study investigators will have access to the final data set and will be eligible for authorship.

This study has limitations that should be considered. Although the sample size is powered for the primary outcome, we do not have the power to detect changes in secondary outcomes or for subgroup analysis to explore the influence of potentially confounding factors. Considering the population under study, there may be an increased risk of attrition due to fatigue or difficulty in scheduling training/testing sessions within the desired time frame. We hope to mitigate these issues by offering validated questionnaire versions of tests and by providing training in the community to overcome transportation challenges associated with commuting to a research center. Given that wheelchair configuration and positioning are outside the scope of the WSTP, we will not consider wheelchair configuration or positioning in this study. However, these factors may have an impact on manual wheelchair skill performance and capacity, and ultimately on the efficacy of the intervention.

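### The interview, where participants are asked about fatigue and perceived dosage, is timed to completing the training, so as written those who start but stop early are not scheduled for it

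*Protocol article*

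**What the plan says.** Two sections of the protocol article set the timing of the interview, and they agree.

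- Study Procedures: "Qualitative interviews will be conducted by the RC by phone or videoconferencing within 7 days of completing the intervention".
- Qualitative Interviews: the interview is held "either in person or online with the RC, after completing the WSTP intervention".

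The Qualitative Interviews section also gives the content: "we will explore perceptions of the WSTP (dosage, fatigue, training approaches, and usefulness" are the topics listed for the training programme.

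Three other places bear on the point.

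- Intervention Details: the trainer will "document adherence to the intervention and any adverse events".
- Data Analysis: "Details of adherence and intervention fidelity will be summarized".
- Limitations paragraph of the Discussion (under Overview): "there may be an increased risk of attrition due to fatigue or difficulty in scheduling training/testing sessions within the desired time frame".

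On the use of the interview material, Data Analysis says that "findings on the facilitators and barriers to training may be transferable to individuals with other neuromuscular disorders".

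**The concern.** The protocol foresees that fatigue may cost it participants, yet it asks participants about fatigue only once training has been completed. Someone who gives up after two sessions because the training was too tiring does not reach the trigger. That person holds some of the most useful information on dose and barriers.

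Three uses of the interviews are exposed:

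- the themes on fatigue, dosage and usefulness;
- the planned exploration of why some participants do better and how people cope with difficulties;
- the statement that barriers and facilitators may carry over to other neuromuscular disorders.

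The integration step is exposed too. Data Analysis gives priority to intention to treat with multiple imputation, so early stoppers stay in the quantitative results. If they are absent from the interviews, the joint displays set a result for everyone randomised beside accounts from completers only, and nothing tells the reader so.

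**Working it through.** This is mainly a matter of setting the sections side by side. The arithmetic only shows how many people could be involved.

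**1. What triggers an interview?** Completing the training, in both sections that address it. No section describes an interview for someone who stops early. Completion is not defined. Control Group describes the five sessions as a target, which leaves open whether fewer sessions can count as complete.

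**2. Where are participants asked about fatigue or dosage?**

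| Source | Asks the participant about fatigue or dosage? | Depends on completing training? |
|---|---|---|
| WST-Q-M (primary) | No: skill performance | No |
| WST capacity | No: observed skills | No |
| WheelCon-M | No: confidence | No |
| Actigraphy | No: movement counts | No |
| Trainer's record | No: adherence and adverse events, written by the trainer | No |
| Interview | Yes | Yes, as written |

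The interview is the only row with a yes in the middle column, and also the only row that depends on completion.

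**3. Does the protocol expect early stoppers?** The limitations paragraph gives two possible causes of attrition, fatigue and scheduling, without ranking them. Its mitigations are questionnaire versions of tests and training in the community. Both aim to prevent loss. Neither gathers the views of those who are lost.

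**4. How many people could this be?** The plan's own figure first: Sample Size needs 18 and allows 10% attrition, so 18 / (1 − 0.10) = 20, which reproduces the stated total. The allowance is 20 − 18 = 2 people.

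The protocol gives no rate for stopping training. Assume, for illustration only, that all 20 start training (the control arm does so after T2), that each stops early with probability p, and that they do so independently. The chance of at least one early stopper is 1 − (1 − p)^20:

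- p = 0.05: 1 − 0.95^20 = 0.64, with 20 × 0.05 = 1 expected;
- p = 0.10: 1 − 0.90^20 = 0.88, with 2 expected;
- p = 0.20: 1 − 0.80^20 = 0.99, with 4 expected.

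So the situation is likely to arise at least once across this range, but it would concern only a handful of people.

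**5. Can the distortion be expressed as a rate?** No. The plan uses reflexive thematic analysis, which does not estimate how common an experience is. A contrast such as 0 of 18 interviewed against 2 of 20 trained would require every stopper to have stopped because of fatigue and no completer to report limiting fatigue. The document supports neither assumption. The direction can be argued; the size cannot be calculated.

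**The case against.** The case on the other side is substantial.

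- **Tolerability is recorded elsewhere.** A reader might infer that nothing else captures it. That is wrong: the trainer documents adherence and adverse events whether or not the participant finishes, and adherence is summarised. What remains is narrower. That record is made by the person delivering the training, and the article does not say that it covers fatigue, perceived dosage or reasons for stopping.
- **The sentences state timing and exclude nobody.** This is fair. A reader might infer that early stoppers will never be heard and that tolerability is bound to look better than it is; the text does not go that far. Completing could mean the end of a participant's own training. But the natural reading of two matching sentences is completion of the programme, and nothing provides for any other case.
- **A condensed article leaves such details to the full protocol.** This would carry weight if the article were silent. It states a trigger, twice, and the trigger itself is the problem.
- **Fatigue is not named as the leading cause of loss.** Correct: it stands beside scheduling, covers testing as well as training, and is worded as a possibility.
- **The 10% is study attrition.** Also correct. It may include waitlist participants lost before any training, who have no training experience to describe.
- **Completers can do poorly too.** They can, and they would be interviewed. Poor outcomes are therefore not absent from the interviews; only the accounts of those who stopped are.
- **Reporting two or so early stoppers separately would be thin and could identify them.** This stands, and the remedy should avoid a separate theme report.

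**Conclusion.** The point holds in a limited form. As written, participants who begin training and stop early are not scheduled for the one interview that asks about fatigue and dosage. The themes on fatigue, dose acceptability and barriers may then be more favourable than the experience of all who were trained.

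This rests on two assumptions: that completing means finishing the programme, and that some participants stop for reasons connected with the training. The first is the plain reading; the second is something the protocol itself raises as a possibility.

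The reach is confined to the qualitative findings and their integration with the quantitative results. The primary ANCOVA, the sample size and the intention-to-treat analysis do not change. The change is worth making because it costs little and the protocol means to draw transferable conclusions about barriers.

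**What to change.** In both Study Procedures and Qualitative Interviews, replace completion of the intervention as the trigger with the last session attended, keeping the 7-day window. Then:

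- invite every participant in either arm who attended at least one session, with the interview remaining voluntary;
- ask those who stopped early for their reason, and read it beside the trainer's adherence and adverse event records;
- consider early stoppers' accounts together with those of completers in the thematic analysis and joint displays, without identifying individuals;
- report how many participants stopped early and how many of them were interviewed.

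If the investigators already mean completing as the end of each participant's own training, a sentence saying so meets most of the point.

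The cost is a change of wording and a minor ethics amendment. No extra staff are needed, and there is still at most one interview per participant. Some early stoppers will decline, so the selection is reduced rather than removed, and the reported counts let the reader judge what remains.

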**Figure 1 figure1:**
[figure not shown]
Trial design describing coordination, testing, and experimental procedures. WSTP: Wheelchair Skills Training Program.

### Intervention Details

According to the evidence-based Wheelchair Skills Training Program (WSTP) [29], participants will receive 5 individual 45-minute weekly wheelchair skills training sessions. As previously described by Best et al [26], the training sessions will take place in the community, in and around the participants’ homes and neighborhoods (eg, libraries, shopping centers, museums, and parks), and will be customized according to the participants’ goals. The WSTP provides suggestions for individualizing the approach based on the learner’s impairments (ie, weakness, spasticity, contractures, cognitive impairments, and movement disorders like ataxia, tremor, and chorea). Therefore, specific training considerations can be made regardless of diagnosis. The WSTP sessions will begin with a 5-minute review of goals/progress, followed by a 10-minute warm-up (wheeling activities, random practice of previously learned skills). This will be followed by 20 minutes of attempting new skills, with training on each skill carried over to the next session until the skills are learned or the trainer and participant mutually agree to stop training. The trainer will periodically ask the participant to practice newly learned skills to incorporate variability of practice. Finally, a 10-minute cooldown will take place, during which the participant will practice skills in a self-controlled environment.

The trainer (author EN), a graduate student with training in physiotherapy will receive two 4-hour sessions by experts in manual wheelchair skills training (authors [name], FR, and [name]), which has been shown to improve knowledge and confidence for training wheelchair skills [30]. The trainer will also complete self-guided learning modules, semistructured practice with trained trainers, and the Wheelchair Skills Program Certification Exam [31]. The fidelity of the WSTP administration will be evaluated by a member of the study team not involved in testing or training who will attend 1 training session per participant (randomly throughout the training period). The trainer will also complete a detailed training log, a checklist of standardized steps to be followed during training, and document adherence to the intervention and any adverse events. Formative assessments with the trainer will ensure fidelity.

### Control Group

Participants in the control group will receive the usual care (if any) during a 4-week period. During this time, participants will be considered on a waitlist to receive the WSTP after the completion of the project and may continue or begin any activities provided by therapists or in the community. After completing the T2 evaluations, participants in the control group will complete a target of five 45-minute weekly sessions of the WSTP, delivered by trained personnel as described for the intervention group. While usual care may include some form of manual wheelchair skills training, the evidence suggests that the amount of training received during usual care, according to the Wheelchair Skills Program, is limited [24].

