**Methods:**

This study will use a sequential multimethods design, combining a waitlist randomized controlled trial and qualitative interviews. The participants will include adults who have a diagnosis of ARSACS or MD1 who use a manual wheelchair for mobility. Participants will be randomly assigned to the intervention or control group using a 1:1 allocation ratio. The intervention group will receive 5 manual wheelchair skills training sessions (1-2 sessions/week), while the control group will receive no training. Data will be collected at baseline (T1), after the 4-week intervention (or waiting period for the control group; T2), and 3 months after T2 to assess retention (T3). The primary outcome will be manual wheelchair skills performance. Secondary outcomes will include manual wheelchair skills capacity, self-efficacy, and mobility. Semistructured individual interviews will be conducted to explore participants’ expectations regarding manual wheelchair use, past manual wheelchair experiences, and perceptions of manual wheelchair skills training. Quantitative data will be analyzed using analysis of covariance (ANCOVA), controlling for baseline scores, and qualitative data will be analyzed using reflexive thematic analysis.

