Learning how to use the wheelchair and developing appropriate wheelchair skills are critical to independent mobility and participation [18]. However, wheelchair mobility for people with ARSACS and MD1 remains understudied. Our team recently demonstrated that adults with ARSACS had lower manual and power wheelchair skills but fewer training goals than adults with other diagnoses (eg, spinal cord injury) [19]. This disparity may be attributed to limited training opportunities and low expectations of wheelchair use for individuals with ARSACS [19]. It may be that the progressive nature of ARSACS and MD1 (and other neuromuscular disorders) and the clinical focus on maintaining functional walking have historically taken clinical precedence over wheelchair mobility outcomes.

The World Health Organization suggests training in wheelchair use and follow-up as important steps in wheelchair service provision [20]. Four meta-analyses demonstrate the effectiveness of wheelchair skills training for improving wheelchair skills, use confidence, and participation [20-23]. However, a survey of 68 Canadian rehabilitation centers demonstrated that >50% of therapists spent 2 hours or less on wheelchair skills training and 18% provided no training at all [24]. Moreover, individuals with ARSACS and MD1 do not typically spend periods of time in rehabilitation centers where most wheelchair skills training occurs. The inherited and progressive nature of ARSACS and MD1 means that people receive wheelchairs when they can no longer walk but do not commonly receive additional assessments, training, or follow-ups related to wheelchair use. Given the evidence on the effect of manual (manual wheelchair) skills training in other progressive conditions (eg, multiple sclerosis, Parkinsonism) [22,23], the association between manual wheelchair mobility and the preservation of upper limb function and strength in ARSACS [19], it is likely that evidence-based training could improve manual wheelchair skills, confidence, and social participation for people with ARSACS, MD1, and other neuromuscular disorders. In a pilot study, 3 individuals with ARSACS improved their manual wheelchair skills (between 18% and 30%) and confidence (between 5% and 15%) after 3 hours or less of manual wheelchair skills training [25].

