The overall aim of this study is to evaluate the efficacy of an evidence-based manual wheelchair skills training program for improving safe manual wheelchair mobility in people with ARSACS and MD1. The primary objective is to test the hypothesis that participants who receive manual wheelchair skills training will improve their manual wheelchair performance by at least 20% compared to those in a control group who receive no training. The secondary objectives are to explore the influence of manual wheelchair skills training on wheelchair skills capacity, use self-efficacy, and mobility. Finally, the participants’ expectations regarding manual wheelchair use and the experiences and perceived impact of manual wheelchair skills training on mobility and quality of life will be explored using a qualitative inquiry.

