## Methods

### Study Design

A sequential multimethods randomized controlled trial (RCT) and qualitative interviews will be used, with the RCT reported according to the CONSORT (Consolidated Standards of Reporting Trials) guidelines [26]. Participants will be randomly assigned to the intervention or control group using a 1:1 allocation ratio. A randomization process with undisclosed block size will be created by a statistician who is not otherwise involved in the project. Given the potential benefits of the intervention already reported in our previous studies [22,23], control group participants will also receive wheelchair skills training following a 4-week control period and postintervention data collection (ie, they will be on a “waitlist” for the wheelchair skills training program and receive no intervention during the study period).

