### Participants and Recruitment

Convenience sampling will be used to recruit 20 community-dwelling people with ARSACS or MD1 who use manual wheelchairs. Active recruitment strategies will include recruiting through outpatient services at the local rehabilitation center in Quebec City (CIUSSS-CN). The chief of physiatry (author XR) who has clinical expertise in ARSACS and MD1 will discuss the study with all individuals on his case load who have a diagnosis of ARSACS or MD1 and use manual wheelchairs. In addition, participants from a longitudinal study on ARSACS (completed in 2022) will be contacted and informed of the study. Passive recruitment strategies will include disseminating promotional videos on the social media and websites of Muscular Dystrophy Canada, other collaborators, and community organizations. Participants will be 18 years of age or older; have a diagnosis of ARSACS or MD1; use a manual wheelchair for mobility (≥ 3 times/week for ≥ 8 hours/week); and be able to propel their manual wheelchair at least 10 meters. Individuals will be excluded if they anticipate a health condition or procedure that contraindicates training (eg, surgery) or if they are concurrently receiving or planning to receive other manual wheelchair training during the study.

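### The hypothesis and the eligibility rule say controls get no wheelchair training, but the Control Group section lets them start it during the 4-week wait

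*Protocol article*

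**What the plan says.** All references are to the protocol article.

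- **Introduction, primary hypothesis.** Trained participants are to improve by at least 20% "compared to those in a control group who receive no training".
- **Participants and Recruitment.** People are excluded "if they are concurrently receiving or planning to receive other manual wheelchair training during the study".
- **Control Group.** Controls receive usual care, if any, for 4 weeks and "may continue or begin any activities provided by therapists or in the community". The section then allows for outside training: "While usual care may include some form of manual wheelchair skills training". It adds only that the amount is limited, citing a survey.
- **Study Procedures.** Usual care is not confined to controls: "Participants in the intervention and control groups will continue to receive usual care (if any) during the study".
- **Abstract (Methods) and Study Design.** The Abstract says "while the control group will receive no training". Study Design says that waitlisted controls "receive no intervention during the study period".
- **Introduction, on the survey.** More than 50% "of therapists spent 2 hours or less on wheelchair skills training and 18% provided no training at all". The same paragraph says that people with these two disorders do not usually spend time in the centres where most such training happens, and seldom receive training after provision of the chair.

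**The concern.** The hypothesis promises a contrast with untrained people. The eligibility rule shows that the sponsor wants other wheelchair training kept out for the length of the study. The Control Group section then permits it to start before the primary assessment at T2, and argues that it is limited, not that it is absent. It sets no rule for a control who is offered wheelchair training after randomisation.

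What is at stake is mainly interpretation. The contrast actually delivered is the Wheelchair Skills Training Program (WSTP) plus usual care against usual care on a waitlist. If the result is reported as a gain over no training, the claim names a comparator that the trial may not have had. Outside training in controls could also shrink the measured difference somewhat.

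**Working it through.** **Step 1: do the statements reconcile?**

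| Place | Comparator | Compatible with the Control Group section? |
|---|---|---|
| Abstract | no training, in the same sentence as the study sessions | Yes, if read as no study WSTP |
| Study Design | no intervention, in a remark about waiting for the WSTP | Yes, on the same reading |
| Primary hypothesis | no training, with nothing nearby to restrict it | Not as worded |
| Eligibility | no other manual wheelchair training, current or planned, during the study | Only in part: training first offered after entry is not covered, and the Control Group section permits it |

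The conflict that remains is between the hypothesis and the eligibility rule on one side and the Control Group section on the other. It concerns training begun after entry.

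**Step 2: the plan's own sample size.** The Sample Size section gives d = 1.2, R² = 0.6, α = 0.05, 90% power, N = 18, and 20 after 10% attrition. For ANCOVA with two groups and one covariate, f = (d/2)/√(1 − R²) = 0.6/√0.4 = 0.949. The smallest even N reaching 90% is 16 (power 93.9%), and N = 18 gives 96.4%. Then 18/0.9 = 20. The stated figure is reproduced to within two participants. The comparator wording does not affect it.

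**Step 3: how large could dilution be?** The documents give neither uptake nor gain, so this is an illustration. Assumptions:

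- 20% is read as 20 points, so SD = 20/1.2 = 16.67.
- Nine are analysed per arm; R² = 0.6 as printed; df = 18 − 3 = 15.
- Outside training lasts 2 h, the boundary of the survey category. WSTP time is 5 × 45 = 225 min (Intervention Details), so the ratio is g = 120/225 = 0.533.
- Gain is proportional to time.

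With k of nine trained outside the study, the difference is 20 × (1 − (k/9) × g) if this happens in controls only. If it happens equally in both arms and WSTP participants keep a share r of the extra gain, it is 20 × (1 − (k/9) × g × (1 − r)).

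| Scenario | Difference | Power |
|---|---|---|
| No outside training | 20.0 | 96.4% |
| Controls only, k = 1 | 18.8 | 94.2% |
| Controls only, k = 2 | 17.6 | 91.2% |
| Both arms, k = 1, r = 0.5 | 19.4 | 95.4% |
| Both arms, k = 2, r = 0.5 | 18.8 | 94.2% |
| Both arms, r = 1 | 20.0 | 96.4% |

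**Step 4: compare with the precision of the trial.** The standard error is 16.67 × √0.4 × √(2/9) = 4.97 points. The 95% CI half-width is 2.13 × 4.97 = 10.6 points. The largest loss in the table is 20 − 17.6 = 2.4 points.

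**Step 5: harsher assumptions.** If outside training worked as well as the whole WSTP, power would be 92.3%, 85.3% and 75.0% with 10%, 20% and 30% of controls trained. Nothing in the article suggests uptake or benefit on that scale. If the printed 0.6 were a correlation (R² = 0.36), power at N = 18 would be 84.4% before any outside training. That is a separate matter from the comparator.

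**The case against.** The strongest reply is that the article is coherent if the Methods section is allowed to define the shorthand. In the Abstract and in Study Design the training withheld is plainly the study programme, and a usual-care waitlist is a legitimate comparator. An entry criterion need not be repeated in the section on control care. The phrase about starting activities is general; only the later sentence mentions wheelchair training. Such training should be rare, since planned training is excluded and the Introduction says these patients seldom get it. The survey covers rehabilitation centres and is not tied to a 4-week window.

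Most of this stands. It clears the Abstract and Study Design, and it makes the gap narrow. It does not clear the hypothesis, which carries no such context. Nor does it explain why outside training is excluded for the length of the study at entry and then allowed to begin during the wait.

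Three stronger readings are tempting, and the documents do not support them:

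- *Every mention of no training contradicts the Control Group section.* Two of the three can be read as no study WSTP.
- *Outside training necessarily pulls the T2 difference toward zero.* Usual care runs in both arms, so dilution needs unequal uptake or gains that do not add fully to those of the WSTP. With equal uptake and full additivity there is none.
- *A null result could be blamed on outside training.* A loss of 1 to 2 points would not turn a 20-point effect into a null when the interval extends about 10.6 points either side; imprecision would dominate.

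**Conclusion.** The point holds as a minor inconsistency in how the comparator is defined. The hypothesis and the eligibility rule do not agree with the Control Group section on non-study wheelchair training begun after entry. Confidence is high for the wording and lower for any numerical consequence.

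The likely effect is small: about 1 to 2 points off an assumed 20 if one or two controls receive about 2 hours, with power still above 90%. This rests on assumed uptake, gain proportional to time, 20% read as points, and R² = 0.6 as printed. Outside training in controls cannot produce a false positive, provided that it does not worsen skills. This is not a power problem, and the sample size and analysis need no change. What needs correcting is the match between the contrast claimed and the contrast delivered.

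**What to change.** Choose one of two.

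1. **Extend the sponsor's own exclusion to the wait.** Add one sentence to the Control Group section: participants in both arms are asked not to start non-study manual wheelchair skills training before T2, while all other usual care continues. Cost: at most a 4-week deferral for anyone offered such training.
2. **Name the comparator as delivered.** In the primary hypothesis and the reported conclusion, write usual care (waitlist), without WSTP. The Abstract and Study Design could be aligned for clarity. Cost: a slightly weaker claim. Procedures do not change, which matters because recruitment began in January 2025.

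Under either option, it would help if the unblinded coordinator, not the blinded research assistant, asked both arms at T2 about non-study wheelchair training. The answers would be reported by arm, with everyone kept in the intention-to-treat analysis. This costs one question. It is a supplement: an article may leave such detail to the full protocol, so its absence is not an error.
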